### Sample size

Sample size calculation has been performed through the software ClinCalc [S1 File] estimating the key outcome as the score of the Gilliam Autism Rating Scale (GARS 2) second edition [23, 30]. Sample size has been calculated [27] as the anticipated minimal clinically important differences (MCID) of GARS-2 [23] were estimated as 4.7±1.7 (0–10 Hiva scale converted from 0–126 GARS 2 score) with a baseline of 25% minimal clinical improvement, enrolment ratio 1:1, 80% power, and with the alpha value 0.05, the total sample stands as of 66. For safety we will enroll 70 ASD adolescents with a number of 35 participants in each group.

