### Recruitment and randomization

The researcher will perform a sample frame to pool the samples for the interventional design. The sample frame will be taken from the dataset of the list of maltreated ASD Adolescents of Bangladesh screened by an early population-based household survey. From the sample frame, Participants living in Dhaka will be contacted one by one and will be invited to take part in this trial, thus hospital based-randomization will be ensured. After the pooled sample estimation, concealed allocation to groups will be performed using the “rand” function in Microsoft Excel 2010. Both groups will be treated in two different centers of an organization to ensure an equal level of care is being provided and prevention of cross-contamination of data. In the group allocation process, block randomization will be employed to ensure the balanced recruitment for two groups.

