### Study procedure

After the trial registration is obtained, researchers will start the phone call procedure to estimate the willing participants. As the primary screening of cases of “ASD with malnutrition” performed in the population-based survey, the parents will be directly contacted for participating in the trial. From the computer-based random serial, the first 70 ASD will be pooled for enrollment in the study. On the first day, an assessor blinded to group allocation will further screen and take a pre-test assessment. Then the participant will be treated in a multi-disciplinary approach with the consultation of a nutritionist, physiotherapist (PT), Occupational therapist (OT), and speech and language therapist (SLT). Both structured dietary treatment and regular therapy will be provided as three 45 minutes sessions per week for a total of 12 weeks. After 12 weeks, the post-test data will be obtained by the assessor. There will be a follow-up evaluation after 6 months of post-test. There will be a separate assessor for each of the treatment set-ups. The Consolidated Standards of Reporting Trials (CONSORT) manual will be followed when conducting the study. Fig 2 provides a summary of the study’s methodology.

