### Eligibility criteria

Participants will be recruited if (1) aged between 13 to 18 years, (2) diagnosed as ASD children based on DSM-V criteria [28], (3) malnutrition according to Body Mass Index (BMI) [29], (4) not taking any diet advice or supplement, and (5) willing to participate. On the other hand, participants will be excluded if- (1) respondents provided consent but dropped out within the first week of enrollment, (2) allergy to any gluten-free, casein-free (GFCF), Soya free diet, (3) severe behavioral problems according to Gilliam Autism Rating Scale (GARS-2) [30].

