*Protocol for UD+ RT group*. The group will receive Regular therapy as per the above protocol, but they will not receive any consultations from the nutritionist and will take the usual diet. After completion of the follow-up, they will be advised of the structured diet intervention based on the study result.

*Progression of interventions*. The intervention duration will be 12 weeks. 45 minutes of the session with the ASD Adolescents and their parents will be provided 3 times a week for each therapeutic intervention item. Participants will receive separate sessions for each therapy item (PT, OT, SLT, SD). The progression of interventions will be determined by subsequent professionals.

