### Data analysis

According to the nature of the data, SPSS version 23 for Windows will be used for analysis. The distribution of data will be performed using normality indicators and normality tests such as the Kolmogorov-Smirnov test, and the Shapiro-Wilk test. Descriptive analysis will be performed by mean and standard deviation for the continuous data, and frequency and percentage categorical data. The baseline compatibility, between-group post-test, and follow-up variations among the groups will be assessed using MANOVA or the Multivariate Kruskal-Wallis (MKW) test, depending on the nature of the data. Repeated measure or Friedman’s ANOVA Three measures will be analyzed within-group using an ANOVA, and additional post-hoc analyses will be performed using paired sample t-tests or Wilcoxon tests. We will perform the intention to treat the analysis process for the drop-out of cases taking more than one month of interventions. In the case of a post hoc Bonferroni adjustment, the level of significance P < .05 will be converted to P < .0125.

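### The intention-to-treat rule covers only drop-outs with more than one month of intervention, and first-week drop-out is an exclusion criterion, so early leavers appear to be removed after randomisation

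*Protocol article*

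**What the plan says.** Two rules in the Protocol article decide who is analysed.

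- **Data analysis:** "We will perform the intention to treat the analysis process for the drop-out of cases taking more than one month of interventions".
- **Eligibility criteria, exclusion (1):** "respondents provided consent but dropped out within the first week of enrollment".

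Three statements bear on timing.

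- **Recruitment and randomization:** "After the pooled sample estimation, concealed allocation to groups will be performed using the “rand” function in Microsoft Excel 2010".
- **Study procedure:** "On the first day, an assessor blinded to group allocation will further screen and take a pre-test assessment".
- **Intervention (progression):** "The intervention duration will be 12 weeks".

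Study setting adds that one centre serves the control group and the other the experimental group. No section says that participants who leave at or before one month are analysed as randomised.

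**The concern.** Intention to treat means that every randomised participant is analysed in the assigned arm, whatever treatment was received. Here the label is tied to an amount of treatment received, and an event after enrolment is used to define eligibility.

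This matters because the reasons for leaving early are not the same in the two arms. Only SD families must adopt a gluten-, casein- and soy-free diet and attend separate nutritionist sessions. The Discussion itself describes people with ASD as selective eaters with sensory sensitivities. The arms also attend different centres, which is a further arm-specific reason to leave. If early leavers are dropped, the two analysed groups may no longer be comparable, and the result would still carry the intention-to-treat label. A larger sample does not cure that.

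**Working it through.** **1. Who falls outside the rules**

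| Time of leaving | Rule that applies | Consequence |
|---|---|---|
| First week | Exclusion (1) | Excluded by name |
| After week 1, up to one month | None | Outside the intention-to-treat sentence |
| More than one month | Intention-to-treat sentence | Kept |

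One month is about 4 of 12 weeks, so a drop-out must have had about a third of the programme to be covered.

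**2. Whether this comes after randomisation**

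No single sentence gives the order, so it has to be inferred:

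- Allocation follows pooling of the sample (Recruitment and randomization).
- The day-one assessor is described as already blinded to allocation (Study procedure).
- Each arm is treated at its own centre (Study setting), so the arm must be known before treatment can start.

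Together these place allocation at or before day one. First-week leavers have then been randomised. For those who leave between week 1 and one month, treatment at an arm-specific centre has already begun, so the conclusion does not depend on the day-one detail.

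**3. The plan's own scale**

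Inputs, all from Sample size:

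- Mean and SD: "were estimated as 4.7±1.7 (0–10 Hiva scale converted from 0–126 GARS 2 score".
- Effect: "with a baseline of 25% minimal clinical improvement", so 0.25 × 4.7 = 1.175 points.
- Design: "enrolment ratio 1:1, 80% power, and with the alpha value 0.05, the total sample stands as of 66".

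n per arm = 2 × (1.960 + 0.842)² × 1.7² / 1.175² = 32.9, rounded up to 33. The total is 66, which matches the stated figure with a two-sided alpha (a one-sided alpha gives 52). The target of 1.175 and the SD of 1.7 are therefore the right yardsticks.

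**4. Illustration of bias (assumed inputs)**

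The article gives no drop-out rate and no link between leaving and outcome. Suppose there is no true effect, a fraction f is removed from one arm only, and those removed differ from those retained by g SD. The full-arm mean is (1 − f) × retained mean + f × removed mean, so:

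shift = retained mean − full mean = f × g × 1.7

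| f | g = 0 | g = 0.5 | g = 1 |
|---|---|---|---|
| 10% | 0 | 0.085 (7% of 1.175) | 0.17 (14%) |
| 20% | 0 | 0.17 (14%) | 0.34 (29%) |

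**5. Power (secondary)**

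With all 70 analysed, power is 82.4%. If 10% of the 70 are removed it is 78.3%, and if 20% are removed it is 73.4%. These rates are also assumptions.

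**The case against.** - **The text never says that early leavers are deleted.** This is true. The intention-to-treat sentence is ungrammatical and could be read as naming which drop-outs get special handling while leaving the others unaddressed. Removal is an inference. It is still the natural one, because a one-month threshold has no purpose unless it separates those kept from those not kept, and first-week leavers are excluded expressly.
- **First-week drop-out is counted from enrolment, not from allocation.** The order is not stated in one place, and describing the assessor as blinded could denote a role rather than a sequence. The schedule and flow chart, where the order would normally appear, were not available for this check. The timing is therefore probable for the first-week group, not proved. The gap from week 1 to one month does not depend on it.
- **A reader might infer that the rule favours SD.** The article does not support a sign. That would require SD families to leave more often and SD leavers to have worse outcomes than stayers. The diet burden makes unequal leaving plausible, but fixes neither its direction nor its size.
- **A reader might reach for a worst case.** If exactly the five worst of 35 leave SD and none leave the usual-diet arm, the shift is 0.263 SD × 1.7 = 0.45 points, or 38% of 1.175. Nothing in the article supports that pattern, and exclusion of severe behavioural problems on GARS-2 trims the tail it relies on.
- **A reader might also say that early losses break the sample size.** The article does not describe 66 as completers, and with 30 versus 35 analysed the normal-approximation power is still 79.3%, against 80.2% at 33 versus 33. Power is not the main issue.
- **The analysis plan may deal with this.** Handling of missing data may well be there. The defect, however, is a rule stated wrongly in the protocol, not an omission.

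**Conclusion.** The point holds as a defect in the stated analysis set. Followed as written, the two rules appear to remove participants because of events after allocation and then call the analysis intention to treat. This rests on two inferences: that the one-month threshold is meant to separate those kept from those not kept, and that allocation occurs at or before day one.

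The comparison can be biased. How much, and in which direction, cannot be determined from the article. Under the illustrative assumptions (10–20% removed from one arm, a 1 SD difference), the false difference is 0.17–0.34 points, or 14–29% of the target; it is zero if leaving is unrelated to outcome. No figure in the sample-size section is wrong.

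The correction is worth making promptly. Recruitment has started (Study status), and outcomes not collected from early leavers cannot be recovered later.

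**What to change.** 1. Delete exclusion criterion (1).
2. Replace the intention-to-treat sentence with: *All randomised participants are analysed in their assigned arm regardless of sessions attended, and are invited to post-test and follow-up even if they stop the intervention.*
3. Keep the set with more than one month of intervention only as a labelled per-protocol sensitivity analysis.
4. State in the same place that allocation precedes the first session, if that is the case.

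The method for missing outcomes can be left to the analysis plan. A likelihood-based mixed model with a sensitivity analysis is one option among several; correcting this defect does not require it.

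The cost is a few changed sentences, attempted visits for early leavers, and an estimate that may be less favourable. The planned sample size and the treatments do not change.

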#### Primary outcome variables

*Gilliam Autism Rating Scale (GARS-2)*. The second edition of the Gilliam Autism Rating Scale (GARS-2) will use to assess the behavioral status and overall status of ASD Adolescents. It is a behavioral screening tool for individuals with ASD between 3–22 years of age, based on DSM-IV (Diagnostic and Statistical manual of mental disorder) criteria for ASD. This scale comprises 42 items ranging from 0–126 scores, divided into 3 subscales (stereotyped behavior, communication, and social behavior) [30].

*Anthropometric measurements (AM)*. Anthropometric measurement (AM) will use to measure the nutritional status of the child. Because it is non-invasive and less expensive than other methods, anthropometry, and circumference of the arm, abdomen, and thigh (MUAC) have long been considered nutritional status determiners [34]. BMI [29] of the child and adolescent will be measured as another indicator of nutritional status. As edema and hydration have the potential to affect weight and BMI values, therefore these factors will consider during the determination of these parameters [35]. These parameters will be pictured on the chart to assess nutritional status.

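### The plan promises an intention-to-treat process but names tests that, in standard form, need complete rows, and it names no way for a drop-out without a post-test to enter them

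*Protocol article*

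**What the plan says.** All of the analysis wording is in the Data analysis section of the protocol article.

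- Between groups: baseline comparability and the group differences at post-test and follow-up "will be assessed using MANOVA or the Multivariate Kruskal-Wallis (MKW) test, depending on the nature of the data".
- Within groups: "Three measures will be analyzed within-group using an ANOVA", in repeated-measures or Friedman form, followed by paired t or Wilcoxon tests.
- Drop-outs: "We will perform the intention to treat the analysis process for the drop-out of cases taking more than one month of interventions".

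No imputation method or likelihood-based model is named, and neither is excluded. The section does not say which variables form the multivariate outcome.

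The Primary outcome variables section places GARS-2 and the anthropometric measures under one heading. The latter are BMI and, in a general sentence on nutritional assessment, "circumference of the arm, abdomen, and thigh (MUAC". The abstract lists only MUAC and BMI for nutritional status. GARS-2 is the outcome that set the sample size. Study procedure puts the first assessment after baseline at 12 weeks and the next one 6 months after that.

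**The concern.** The drop-out sentence and the named tests do not fit together as they stand. Someone who leaves after, say, six weeks and does not return has a baseline value only. In standard form none of the named tests can use that person's outcome, yet this is the kind of participant for whom intention to treat is promised.

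Two things are at stake. If nothing fills the gap, the group comparison rests on completers. It then favours the diet arm whenever families of children who do badly on a restrictive diet leave more often. Second, a joint multivariate test can drop a participant's observed GARS-2 score because a different measure is missing.

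**Working it through.** **1. The plan's own figure.** Inputs from Sample size: GARS-2 values that "were estimated as 4.7±1.7 (0–10 Hiva scale converted from 0–126 GARS 2 score", "with a baseline of 25% minimal clinical improvement", and "enrolment ratio 1:1, 80% power, and with the alpha value 0.05".

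- Difference: 0.25 × 4.7 = 1.175. Standardised: 1.175 / 1.7 = 0.691.
- n per arm = 2 × (1.960 + 0.842)² / 0.691² = 32.9, so 33 per arm and 66 in total. This matches "the total sample stands as of 66". Sidedness is not stated; two-sided reproduces the figure, and one-sided would give 52.
- Power with 35 per arm: Φ(0.691 × √(35/2) − 1.960) = 82.4%. This is the ceiling if all 70 give a GARS-2 value.

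**2. What each test needs.**

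| Test | Complete row means |
|---|---|
| MANOVA | every outcome in the vector at that visit |
| Multivariate Kruskal-Wallis | usually the same, but depends on the implementation, which is not specified |
| Repeated-measures or Friedman ANOVA | all three visits of that one outcome |
| Paired t or Wilcoxon | both visits of the pair |

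A participant with baseline only fails every row for post-baseline results. A missing circumference does not affect a repeated-measures test of GARS-2 alone.

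**3. Loss of GARS-2 through another outcome (only if the vector is shared).** In a simulated MANOVA of GARS-2, MUAC and BMI on 70 rows, one missing MUAC left 69 rows; filling the value restored 70. If each of k measures is missing independently with probability m, the share of participants lost is 1 − (1 − m)^k. For k = 3:

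- m = 1%, 3%, 5% gives 3.0%, 8.7%, 14.3%, against 1%, 3%, 5% for GARS-2 alone.
- At m = 5%, 70 × 0.857 = 60.0 participants remain (GARS-2 power 76.3%), against 70 × 0.95 = 66.5 (80.5%).

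**4. Power if incomplete cases are deleted.** With loss d in each arm, 35 × (1 − d) remain. At d = 10%: 31.5 per arm, power 78.3%. At d = 20%: 28 per arm, 73.4%. The spare of 4 in 70 covers 5.7%.

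**5. Bias.** The article gives no drop-out rates, so these are assumptions: no true effect, 35 per arm, between-visit correlation 0.6–0.8, 10% random loss on usual diet, and 20–30% loss on structured diet, more likely with a worse week-12 score (logistic slope 1–2 per SD). One SD is 1.7 × 126/10 = 21.42 raw GARS-2 points.

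| When and why participants leave | Complete-case bias | Model-based bias |
|---|---|---|
| After week 12, on the observed week-12 score (bias at follow-up) | 0.11–0.30 SD (2.4–6.4 points) | within 0.01 SD of zero |
| Before week 12, on the unobserved week-12 score (bias at week 12) | 0.16–0.38 SD (3.4–8.1 points) | 0.06–0.25 SD (1.3–5.4 points) |

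All biases favour the diet arm. In the first row a complete-case test at 5% rejects in about 7–21% of trials. The model uses all observed visits in the first row; in the second, only baseline is available to adjust for.

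**The case against.** The strongest reply is that the article never says incomplete cases are deleted. An intention-to-treat process may well mean imputation, and a condensed article may leave that method to a fuller document. This stands, and it rules out a tempting stronger reading: that the plan removes these participants and labels a complete-case analysis as intention to treat. The text supports only that the named tests cannot include such a participant unless values are filled in.

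Other limits also stand:

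- Someone who stops sessions may still be assessed at week 12, so not every drop-out lacks a post-test.
- A reader might infer that any single missing value removes a participant from every test. Deletion applies only to the variables and visits in that analysis.
- The shared outcome vector is inferred from the outcome headings. A five-measure vector is weaker still, since the abstract lists only MUAC and BMI. Independent missingness is also unfavourable, because measures taken at one visit tend to be missing together.
- The Discussion's remark on sensory sensitivity concerns eating, so it is no evidence that participants will refuse a tape measure.
- The three-visit tests are within-group, so they do not carry the group comparison.
- The simulation with loss after week 12 meets the model's own assumption, so near-zero bias is expected there. The quoted sentence concerns people who leave during the intervention, where the gain is partial.

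What the reply does not remove is that the article itself chose these tests and itself promised intention to treat. A model that uses incomplete records directly is a better primary choice than complete-row tests plus an unnamed repair.

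**Conclusion.** The concern holds in limited form. As written, the promised process and the named tests are joined by nothing in the text, and for a drop-out not assessed at post-test those tests cannot deliver it without imputation. Loss of GARS-2 scores through a missing anthropometric value is conditional on a joint vector.

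The size depends on assumed drop-out. With 10% against 20–30% loss, a mixed model removes a complete-case bias of about 0.11–0.30 SD if loss follows an observed week-12 score. If participants leave earlier because of an outcome nobody observed, it only reduces the bias, from about 0.16–0.38 SD to 0.06–0.25 SD. A reader might infer that the mixed model alone solves the problem; the second case shows it does not. With equal or unrelated losses the cost is mainly power: 82.4% falls to 78.3% at 10% deletion.

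This should be changed before analysis.

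**What to change.** In Data analysis:

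1. Make the between-group analysis of GARS-2, and of each anthropometric outcome separately, a mixed model for repeated measures on all randomised participants with all observed visits. Fit arm, visit, arm × visit and baseline. Omit no observed value because another outcome or visit is missing.
2. Say that this is the intention-to-treat analysis, and keep any MANOVA as secondary.
3. Add one sensitivity analysis for informative drop-out, such as delta-adjusted multiple imputation. With baseline as a covariate, a participant who has a baseline value only adds almost nothing to the model, so this analysis is where such participants are properly represented.

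The cost is analysis wording, one model available in SPSS 23 and one extra analysis. No new data or participants are needed. The downside is that the model assumes data are missing at random, which is why step 3 is needed.

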There have been several systematic reviews and meta-analyses [14–16] conducted on the nutrition of ASD children. There are different opinions on dietary interventions for ASD in Adolescents [12, 17, 18]. It is assumed that gluten-free and casein-free diets can minimize the symptoms of ASD, but there are controversial theories about the effectiveness of the gluten-free and casein-free (GFCF) diet [17]. According to certain studies, the GFCF diet can assist with symptoms such as stereotyped attitude, cognitive and social function, attention, interaction, and mood [18]. Many explanations have been proposed to explain how the GFCF diet improves the features of autism. Of all of these, the opioid excess hypothesis is the most widely accepted. Gluten and casein both affect the central nervous system via the leaky gut, but opioids escape via inflamed and thinning stomach in children with ASD [12].

Therapeutic interventions are multidisciplinary approaches [19] that, composed of balance [20], gait training [21], Therapeutic horse riding [22], motor training [23], strength training [24], aerobic exercise [25], and executive functional tasks [26]. It is hypothesized that structured dietary intervention adjunct with regular treatment approaches may have a greater benefit in children with ASD but no such research in Bangladesh has been held yet. It is important to determine the combined outcome of a structured diet (SD) and regular therapy (RT) for improving nutritional status and behavioral indices in the child and adolescents with malnutrition having Autism in Bangladesh.

The study objectives are to (1) determine the socio-demographics and anthropometric measures related to malnutrition for ASD in Bangladesh, (2) to elicit the within-group difference between structured diet (SD) with regular therapy (RT) or usual diet (UD) with regular therapy (RT) therapy on nutritional status and behavioral indices in post-test (3months) and follow-up (6months) compared to baseline, and (3) to find out the effectiveness among groups (SD with RT versus UD with RT) and observations (pretest to post-treatment, pretest to follow up, and post-test to follow up) comparison in the improvement of nutritional status and behavioral indices.

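### Several unranked primary outcomes are compared between groups at two visits with no primary visit and no error control across visits or for outcome-level tests; the one adjusted level stated (.0125) has no defined family

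*Protocol article*

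**What the plan says.** **Outcomes.** Under the plural heading Primary outcome variables, the protocol article lists GARS-2 and then anthropometry. For anthropometry it states that "circumference of the arm, abdomen, and thigh (MUAC) have long been considered nutritional status determiners", and it adds BMI as a further nutritional indicator. None is ranked above another. The Sample size section, by contrast, works from one outcome, "estimating the key outcome as the score of the Gilliam Autism Rating Scale (GARS 2) second edition", and concludes "with the alpha value 0.05, the total sample stands as of 66".

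**Between-group analysis.** Data analysis assigns baseline comparability and the group comparisons at post-test and follow-up to MANOVA or a multivariate Kruskal-Wallis test. It names no primary visit. It gives no rule for two visits, and none for outcome-by-outcome tests after a significant multivariate result.

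**Within-group analysis.** The three measurements are analysed by repeated-measures ANOVA or Friedman's test, with paired t or Wilcoxon tests as post hoc comparisons. The section closes with "In the case of a post hoc Bonferroni adjustment, the level of significance P < .05 will be converted to P < .0125". The third objective (end of the Introduction) lists three time contrasts: pretest to post-test, pretest to follow-up, and post-test to follow-up.

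**Timing.** The second objective speaks of differences "in post-test (3months) and follow-up (6months) compared to baseline". Study procedure says "There will be a follow-up evaluation after 6 months of post-test", and the Abstract agrees with Study procedure.

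**The concern.** The comparison that answers the trial's question is the difference between the two diet groups. For it, the plan fixes neither which outcome nor which visit decides. If GARS-2, a circumference or BMI, at either visit, may each count as a primary success, a result can be claimed on whichever one crosses 0.05, and the error rate of that claim is not 5%.

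The one adjusted level that is stated does not fill the gap. It stands after the within-group post hoc tests, which measure change over time in each arm and do not estimate the effect of the diet. Its divisor of 4 also disagrees with the three contrasts in the objectives. A reader cannot tell which four tests are meant, or whether the level is also to be used between groups.

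**Working it through.** **1. The plan's own sample size.** Inputs from Sample size: mean 4.7 and SD 1.7 on the converted 0–10 scale, 25% improvement, "enrolment ratio 1:1, 80% power", alpha 0.05. Sidedness is not stated. Reading 25% as a fraction of 4.7, the difference is 0.25 × 4.7 = 1.175.

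n per arm = 2 × (z₀.₉₇₅ + z₀.₈₀)² × (SD/difference)² = 2 × (1.960 + 0.842)² × (1.7/1.175)² = 32.9, rounded up to 33, so 66 in total.

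This matches the stated 66. The one-sided version gives 52 and does not. The calculation therefore corresponds to a single two-sided test of GARS-2 at 0.05.

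**2. The divisor behind .0125.** 0.05/0.0125 = 4. Three visits give 3 × 2/2 = 3 pairwise contrasts, the same three as in the objectives, and 0.05/3 = 0.0167.

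Using .0125 for three contrasts gives a family-wise error of at most 3 × 0.0125 = 0.0375, or 1 − 0.9875³ = 0.037 if independent. The mismatch is conservative for one outcome in one arm.

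**3. Family-wise error of the between-group comparisons.** Each test is taken at 0.05.

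| Family | Formula | If independent | With assumed correlation |
|---|---|---|---|
| One omnibus test at each of 2 visits | 1 − 0.95² | 9.8% | about 8.5–9.2% |
| 3 outcomes × 2 visits, tested singly | 1 − 0.95⁶ | 26.5% | about 20–25% |

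The last column is a simulation under the global null. It assumes a between-visit correlation of 0.5 to 0.7, a MUAC–BMI correlation of 0 to 0.8, and GARS-2 uncorrelated with both. The documents give no correlations. The count of three treats the circumferences as one outcome.

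**4. What .0125 would do if it governed the GARS-2 group comparison (hypothetical).** With the same difference and SD:

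- n per arm = 2 × (2.498 + 0.842)² × (1.7/1.175)² = 46.7, rounded up to 47, so 94 in total.
- With the 35 per arm to be enrolled, power is 65.3% by the normal approximation (62.8% by noncentral t), against 82.4% (81.3%) at 0.05.

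**5. Follow-up date.** Six months after a 12-week post-test is about nine months from baseline. The bracketed months in the second objective, set beside three months for the post-test, can be read as six months from baseline. They can also be read as six months after the post-test, with baseline only as the comparator.

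**The case against.** **The between-group test is multivariate.** This is the strongest point on the other side, and it stands in part. If the outcomes enter MANOVA jointly, one omnibus test per visit controls error across outcomes at that visit. A reader might infer that the group comparisons have no protection at all and a 26% error rate; Data analysis does not support that, because it does not plan six separate tests. Two gaps remain. Nothing controls error across the two visits. And a significant omnibus result does not say whether behaviour or nutrition improved, so outcome-level tests must follow, and no rule covers them.

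**The .0125 level need not equal the design alpha.** This stands. The level is tied to post hoc testing, while 0.05 belongs to the GARS-2 calculation. A reader might infer that the trial is underpowered at about 63–65%. No text applies .0125 to the GARS-2 group comparison, so that loss is conditional.

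**Four may have a source.** The Abstract names four measures: the Childhood Autism Rating Scale, MUAC, BMI and GARS-2. Dividing by four could refer to them, but Data analysis does not say so, and the first of them is not among the primary outcomes. What is established is an undefined family, not a proven miscalculation.

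**GARS-2 is already the key outcome.** Sample size says so, which points to one main outcome, but neither the outcome section nor the analysis carries it through.

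**Detail of this kind belongs in an analysis plan.** Testing procedures often do. But this article itself fixes several primary outcomes and a specific threshold, and these do not fit its sample size and objectives.

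**The follow-up wording can be reconciled.** This stands. The Abstract and Study procedure agree, and the objective is ambiguous; it is not a clear contradiction.

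**Conclusion.** The point holds as a defect of specification in the confirmatory analysis. Several outcomes are primary without ranking, two post-baseline visits are compared with no primary visit, and error is not controlled across visits or for outcome-level tests after the omnibus test.

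Read as written, with outcomes entered jointly, the family-wise error is up to about 9.8% for two independent omnibus tests, and somewhat less with correlated visits. The 26% figure is an upper illustration that applies only if three outcomes are tested singly at both visits and are independent.

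The .0125 level is unexplained and does not match the three stated contrasts, but it errs on the safe side (at most 3.75%). It should not be read as inflating type I error, and it threatens power only if someone applies it to the GARS-2 group comparison.

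The reproduction of 66 rests on reading 25% as a fraction of 4.7 and on a two-sided test. The exact match supports both.

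**What to change.** 1. Declare the between-group difference in GARS-2 at one visit as the single primary comparison, at two-sided 0.05. The 12-week post-test is the natural choice because it closes the intervention period, though the Sample size section names no visit.
2. Make MUAC or other circumferences, BMI and all follow-up comparisons secondary, tested by Holm or in a fixed sequence once the primary is significant.
3. State that .0125 does not apply to the primary test. For the within-group time contrasts, either use 0.05/3 = 0.0167 or define the family of four that .0125 stands for.
4. Reword the second objective so that the follow-up date agrees with the Abstract and Study procedure, counted from one stated origin.

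**Cost.** No added participants: the existing 66 (70 enrolled) was computed for exactly this primary test. MUAC and BMI lose primary status, which is a change of substance in a trial that also aims at nutrition. The Study status section says recruitment has started, so this needs a dated protocol amendment, made before any outcome data are examined by group.
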